## Abstract

**Background:**

Cancer is the second leading cause of death globally. Early detection and disease management lead to a better survival rate. Consequently, discovery of novel methods in cancer early diagnosis is a field of active research. Minimally invasive liquid biopsies are generating growing interest. Circulating tumour cells (CTCs) have been identified in patients’ blood; nevertheless, these cells are rare and heterogeneous. Exosomes are extracellular nanovesicles released into the extracellular environment via the endosomal vesicle pathway and found in different body fluids. Exosomes deliver bioactive cargo such as proteins, mRNA and miRNA to recipient cells in the tumour environment. We have recently shown that heat shock protein 70 (HSP70) is detected in the membrane of tumour-derived exosomes, in contrast to normal cells. One single cancer cell can release thousands of HSP70-exosomes, facilitating detection. The aim of the pilot study ExoDiag is to determine whether it is possible to detect and quantify HSP70-exosomes in blood in patients with solid cancers.

**Methods:**

Bicentric pilot study that will include 60 adult patients with metastatic and non-metastatic solid tumours and 20 healthy volunteers. Exosomes will be isolated from blood and urine samples, and HSP70 concentration will be determined. Patients will be followed for 1 year. The study is sponsored by Georges-François Leclerc Centre and is currently ongoing.

**Discussion:**

We expect to demonstrate that HSP70-exosomes could be a powerful tool to diagnose cancer and to guide clinicians in therapeutic decision-making, improving patient’s care.

**Trial Registration:**

ClinicalTrials.gov identifier NCT02662621. Registered 20 January 2016, https://clinicaltrials.gov/ct2/show/study/NCT02662621?term=NCT02662621&rank=1

## Background

Cancer is one of the most lethal diseases due to lack of early diagnosis. In 2018, the global cancer burden is estimated to 18.1 million new cancer cases and 9.6 million cancer deaths worldwide, according to the International Agency for Research on Cancer (IARC) [1]. In France, prostate and breast cancer are the most common cancers among men and women, respectively. Lung, colon, and breast cancer represent more than one third of cancer-related deaths [1]. In 20 years, cancer death rate decreased 22% in men and 14% in women (INCa). This decrease is correlated not only to treatment improvement but also to earlier diagnosis. It is well known that development of efficient diagnosis methods is crucial to reduce the cancer-related morbidity.

Current solid biopsy methods of tumour tissues are critical for the diagnosis and molecular testing of cancer. Nevertheless, several limitations have been observed in current sampling methods such as invasiveness, recovery of a limited amount of biomaterials and difficulties in repeated sampling. Moreover, tumour heterogeneity may render difficult representability of a particular tumour tissue biopsy [2, 3]. Therefore, liquid biopsies, collecting body fluids such as blood, urine, effusions or saliva, through a minimally invasive method are currently tested to identify biomarkers relevant for cancer diagnosis and dynamic monitoring.

Circulating tumour cells (CTCs) have been identified in blood. These cells are extremely rare, 1 CTC to 10^6^–10^7^ leukocytes, in particular in early stage disease [4]. A test to detect CTCs of epithelial origin has been approved by FDA [5]; nevertheless, this technique has not been implemented into routine clinical practice [6]. Indeed, epithelial cell adhesion molecules used to detect CTCs are not present at the surface of all CTCs.

Exosomes are nanovesicles (diameter 50–200 nm) secreted by numerous cell types and derived from the endosomal pathway. These extracellular nanovesicles form a bioactive cargo retrieved in several body fluids including the urine [7] and blood [8].These vesicles are composed of a cholesterol-enriched membrane enclosing proteins and genetic material. It has been shown that tumour-derived exosomes play an important role in cancer development [9]. We have shown that heat shock protein 70 is detected in the membrane of tumour-derived exosomes, in contrast to untransformed cells [10]. HSPs, also called stress proteins, are highly conserved molecular chaperones that participate in protein folding, activity, transport and stability [11, 12]. Among the different HSPs, HSP70 is induced by different types of stress and exhibits cell protective properties through its interaction with key factors in cell death pathways. HSP70 has an anti-apoptotic function, and its overexpression in cancer cells [13] confers resistance to chemotherapeutic drugs, thereby promoting cancer development [14]. Therefore, HSP70 expression level may predict chemotherapy response [15]. Indeed, HSP70 expression correlates with poor prognosis in breast, prostate, endometrial, uterine, cervical and bladder carcinomas [16]. Interestingly, HSP70 can be released in the extracellular space acting like danger signal [17]. Moreover, this protein can be expressed in a membrane-bound form, exposing in the extracellular media a 14 amino-acid C-terminal loop. We have demonstrated that HSP70 can be secreted via exosomes. In contrast to normal cells/untransformed cells, overexpression of HSP70 in cancer cells leads to its membrane translocation and its consequent detection in exosome surface. We have named these nanovesicles HSP70-exosomes [10, 18]. Their involvement in tumour growth through inhibition of the immune response and enhancement of metastatic niche formation has been demonstrated [14, 19]. These data prompted us to test whether HSP70-exosomes could be used as a cancer biomarker. Detection of HSP70-exosomes in the urine and blood of cancer patients could overcome limitations observed with CTCs since (i) exosomes are found in large amounts compared to CTCs (e.g. 53.2 ± 1.6 × 10^8^ exosomes per 10^6^ cells in the 24 h period, determined by Nanoparticle Tracking Analysis [20], (ii) HSP70 is broadly expressed in cancer cells and its overexpression in these cells leads to its membrane translocation and consequent detection in the exosomal membrane. (iii) We have patented an interference biolayer (BLI) protocol to easily capture HSP70-exosomes isolated from human fluids using as a high affinity ligand our peptide aptamer A8 (WO2015/189395, Inserm transfer, 2014).

Multiple clinical studies are currently ongoing to investigate the use of exosomes as a diagnosis tools in the context of specific cancer subsets. In this study, we will test whether detection and quantification of HSP70-exosomes in a liquid biopsy of patients suffering from different types of solid tumours could be used to cancer early detection, to predict response to treatment and to allow disease monitoring. This approach could provide a novel, non-invasive, sensitive and fast method in diagnosis and dynamic monitoring of cancer.

## Methods

### Study population

Sixty adult patients with either non-metastatic or metastatic solid tumours will be included in the study. Briefly, 30 women with breast cancer whose, (i) 10 HER2-positive (5 non-metastatic and 5 with a first metastatic evolution), (ii) 10 HER2-negative (5 non-metastatic and 5 with a first metastatic evolution), (iii) 10 on hormone replacement therapy (5 non-metastatic and 5 with a first metastatic evolution), 10 women with an ovarian cancer grade III and IV, 10 men and 10 women with a metastatic non-small cell lung cancer and 20 healthy donors will be included in the study (Fig. 1). Eligibility criteria for cancer patients are listed in Table 1. Additionally, 20 healthy volunteers with no previous cancer history, negative serology for HIV, HCV and HBC and aged 50 to 70 years old will also be included. Age group of healthy donors is in agreement with the average age of occurrence of the different solid tumours studied.

**Fig. 1 Fig1:**
[figure not shown]
Study population

**Table 1 Tab1:** EXODIAG study inclusion and exclusion criteria for cancer patients

Inclusion criteria for cancer patients	
Women newly diagnosed with infiltrating non-metastatic breast cancer (positive or negative HER status or hormone therapy). Women with breast cancer with a first metastatic evolution (positive or negative HER status or hormone therapy).	
Women newly diagnosed with stage III and ICV ovarian cancer. Men and women newly diagnosed with metastatic non-small cell lung cancer.	
Patients older than 18 years. Performance status of 0 or 1 at the time of inclusion, according to the Eastern Cooperative Oncology Group (ECOG) and WHO.	
Affiliated to the French social security social or beneficiary of such a regimen.	
Written informed consent.	
Exclusion criteria for cancer patients	
Patient with another synchronous tumour.	
Men with breast cancer.	
Positive serology for HIV, HCV or HBV.	
Patients unable to undergo medical follow-up for geographical, social or psychological reasons.	
Pregnant or nursing women.	

### Study objectives and endpoints

The primary objective of this study is to determine whether it is possible to detect and quantify HSP70-exosomes in blood in patients with solid cancers.

The secondary objectives are to:
determine whether the amount of HSP70-exosomes can be associated to:(i)response to treatment;(ii)metastatic evolution;2.determine whether the concentration of HSP70-exosomes varies with the nature of the primary tumour or the effectiveness of the treatment used;3.compare the concentrations and the early detection in HSP70-exosomes and those in circulating tumour cells determined by CellSearch, at inclusion and during patient follow-up;

The primary endpoint of the study is the blood concentration of HSP70-exosomes in malignant solid tumour patients and cancer-free controls. The secondary endpoints are as follows:
(i)the concentration of blood HSP70-exosomes in patients having a complete response, partial response, stable disease or progressive disease (RECIST criteria);(ii)the concentration of blood HSP70-exosomes in patients having metastases versus non-metastatic patients;

This study includes optional ancillary studies whose aims are to detect and quantify HSP70-exosomes in patients’ urine and to determine the genetic signature of miRNAs in HSP70-exosomes isolated from patients’ blood and urine and whether these miRNAs can be predictive of treatment response.

### Study design

Investigator will provide eligible patients with an informative notice on ExoDiag study. Upon patient written consent, serology to HIV, HCV and HBV will be tested (Fig. 2). Only patients with negative serology for these infectious agents will be included, to protect technicians from biological risks, in agreement with laboratory procedures. During the study, 10 ml of blood, collected in an EDTA tube, will be necessary for each exosomal HSP70 analysis, and additional 10 ml of blood, collected with preservative cell save (Cell Search®) will be required for each CTCs analysis. Study design is depicted in Fig. 2.

**Fig. 2 Fig2:**
[figure not shown]
Study design

#### Initial sampling

Prior to any treatment (radiotherapy, hormone therapy, surgery or chemotherapy) blood will be collected for exosomal HSP70 and CTCs analysis (Fig. 2; patients D1C1, Day1Cure1).

#### Follow-up

Sample collection schedule will depend on treatment standard of care (Fig. 2; patients follow-up D1C(x), Day1CureX):
Upon a surgical treatment, initial follow-up blood sample for HSP70 analysis will be collected during the planned post-surgery visit to the investigator site;Upon hormone therapy, blood sample for HSP70 analysis will be collected at each follow-up oncology visit, in average every 6 months;Upon chemotherapy, blood sample for HSP70 analysis will be collected every two cures (C2, C4, C6, C8); sample schedule will be maintained even if toxicity leads to treatment changes.

#### Disease progression

If disease progression is observed, blood will be collected for exosomal HSP70 and CTCs analysis (Fig. 2, patients-tumour progression).

#### Healthy donors

Blood samples will be collected every 3 months during 1 year (V1 to V4) for exosomal HSP70 analysis in healthy donors (Fig. 2, healthy donors). Moreover, in the event of cancer, healthy donors will be removed from the analysis and replaced.

#### Ancillary studies

Patients and healthy subjects will be informed on ancillary studies. Such studies will not require additional visits. If participant agrees to participate, 20 ml of first-morning specimen urine will be collected for exosomal HSP70 analysis, and additional 22.5 ml of blood (5 EDTA tube 4.5 ml) will be collected to study miRNA content of HSP70-exosomes.

### Sample analysis

Extracellular vesicles will be isolated by ultracentrifugation and characterised using a standardised protocol. Particle concentration and distribution profile will be assessed using Nanoparticles Tracking Analysis (Nanosight NS300). Expression of specific exosomal markers will be analysed by western blot. HSP70-exosomes will be captured by Biolayer Interferometry using the A8 aptamer (WO2015/189395, Inserm transfer, 2014), and HSP70 concentration will be quantified by ELISA.

### Data collection

Data collected during the study will be recorded on a CRF for patients and healthy donors. On initial visit, age, sex, weight, height, medical history and special medication will be noted. In addition, healthy donors will be followed for a year and any change in treatments or intercurrent illness. Concerning patients, upon diagnosis and during medical follow-up, date of disease diagnosis, line of treatment, date and relapse type, metastasis/metastatic sites, surgical procedures, treatment modification, date of medical exams performed during assessments (radiographic, biological) and date of death will be noted.

### Sample size and statistical analysis

A selected group of 60 patients, including 30 women with a breast cancer whose (i) 10 HER2-positive (5 non-metastatic and 5 with a first metastatic evolution), (ii) 10 HER2-negative (5 non-metastatic and 5 with a first metastatic evolution), (iii) 10 on hormone replacement therapy (5 non-metastatic and 5 with a first metastatic evolution), 10 women with an ovarian cancer grade III and IV, 10 men and 10 women with a metastatic non-small cell lung cancer and 20 healthy donors will be included in the study (Fig. 1). In this project, the main objective is to evaluate the feasibility of HSP70-exosomes dosing in patients with cancer: The assumptions related to baseline assays are as follows: a technically feasible dosage rate of 75% is considered to be insufficient, a 90% feasibility rate is expected, unilateral alpha = 5%, power = 90%, 10% rate of withdrawal of patient consent or study discontinuation before initial dosing. Based on these assumptions, using a one-step Fleming design, 60 subjects are required (55 + 10% = 60). At the end of the study on the first 55 patients included, if 47 or more patients had a dosage, the technique will be considered as having good feasibility.

In addition, baseline assays of the 60 patients will be compared with 20 controls, to confirm that exosome HSP70 is as a cancer specific marker. The mean of HSP70 in the controls is expected to be 0. It is expected to be around 2 for cancer patients with a common standard deviation of 2. With these hypotheses, bilateral alpha of 5% and 60 patients, we will have a power of more than 95% to compare exosome HSP70 concentrations between cases and controls.

Subgroup analyses, depending on the pathology, histological type and response to treatment, will be exclusively exploratory. These analyses will be carried to study whether variations in HSP70-exosome dosage at baseline and follow-up could be associated with these different variables.

In exploratory analysis, association between HSP70-exosomes concentration and treatment response (response and stable versus progressive disease) will be modelled using logistic regression and ROC curves. Area under the ROC curve will be determined with its 95% confidence interval. The same strategy will be applied to determine link between HSP70-exosomes concentration and the presence of metastases. Analyses will be repeated on subpopulation according to location of the cancer. Analyses will be performed using SAS 9.4.

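### The feasibility rule of 47 out of 55 has its 90% power only with 55 assayed patients, which 60 enrolled with 10% loss and a count of patients included do not secure

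*Protocol article*

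**What the plan says.** All of this stands in the protocol article, Methods, Sample size and statistical analysis, which names feasibility of the baseline assay as the main objective. (The article uses dosage and dosing for the HSP70-exosome measurement.)

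- Unacceptable rate: "a technically feasible dosage rate of 75% is considered to be insufficient".
- Target rate: "a 90% feasibility rate is expected".
- Error rates: one-sided alpha 5%, power 90%, "using a one-step Fleming design".
- Loss allowance: "10% rate of withdrawal of patient consent or study discontinuation before initial dosing".
- Enrolment and the set on which the decision is taken: "60 subjects are required (55 + 10% = 60). At the end of the study on the first 55 patients included".
- Decision: feasibility is good if at least 47 of those patients have a result.

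The section does not say whether a patient who leaves before the assay is replaced within the 55, left out, or counted as having no result. It gives no cut-off for fewer than 55.

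**The concern.** The threshold, the enrolment target and the loss allowance are all stated, and they do not fit together.

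First, the inflation is short, so on the plan's own loss assumption the number for which the cut-off was derived will more often than not fail to be reached. Second, the extra patients are there to make good those lost before the assay, yet the decision is tied to "At the end of the study on the first 55 patients included", a group that on its face still contains the lost patients.

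This is the only decision rule the article gives for its main objective, and the Discussion makes an international multicentre study conditional on the pilot succeeding. A technique that works in 90% of samples could be declared not feasible more often than the stated 10%. The same data could also pass or fail depending on who is counted. For example, 46 results from 50 assayed patients (92%) would miss a fixed 47 but clear the exact cut-off for 50, which is 43.

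**Working it through.** **Inputs**, all from Sample size and statistical analysis: p0 = 0.75, p1 = 0.90, one-sided alpha 0.05, power 0.90, loss before the assay 0.10, enrolment 60, rule at least 47 of 55. Below, X is the number of patients with a result, and P(X ≥ r | n, p) is the exact binomial tail.

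**1. The plan's own design reproduces.**
- Alpha: P(X ≥ 47 | 55, 0.75) = 0.0454.
- Power: P(X ≥ 47 | 55, 0.90) = 0.9056.
- No smaller n meets both targets exactly. The normal approximation, n = [(1.645·√(0.75·0.25) + 1.282·√(0.90·0.10)) / 0.15]², gives 53.5.

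**2. The inflation.**
- To keep 55 after 10% loss: 55 / 0.90 = 61.1, so 62.
- Simply adding 10%: 55 × 1.10 = 60.5, so 61.
- Expected to remain from 60: 60 × 0.90 = 54.
- Chance that at least 55 of 60 remain: P(X ≥ 55 | 60, 0.90) = 0.437.

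**3. The rule at the expected 54.**

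| Cut-off at n = 54 | Alpha | Power |
|---|---|---|
| 47 | 0.0241 | 0.832 |
| 46 | 0.0525 | 0.914 |

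Only 47 respects 5%, so power at the expected number is 83%.

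**4. Averaged over random withdrawal.** Let M ~ Bin(60, 0.90) be the number assayed. Apply 47 to the first min(M, 55):

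Σ P(M = m) · P(X ≥ 47 | min(m, 55), p)

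This gives power 0.744 at p = 0.90 and alpha 0.026 at p = 0.75.

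**5. Worst-case literal reading.** The first 55 included are counted, and those lost before the assay score as having no result.
- At p1: 0.90 × 0.90 = 0.81, and P(X ≥ 47 | 55, 0.81) = 0.258.
- At p0: 0.75 × 0.90 = 0.675, and P(X ≥ 47 | 55, 0.675) = 0.002.
- The result depends strongly on the loss rate: power is 0.80 with 2% loss and 0.60 with 5%.

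**6. With a cut-off matched to the number assayed.** Take the smallest r with P(X ≥ r | n, 0.75) ≤ 0.05:

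| n | 50 | 51 | 52 | 53 | 54 | 55 | 56 | 57 | 58 | 59 | 60 |
|---|---|---|---|---|---|---|---|---|---|---|---|
| r | 43 | 44 | 45 | 46 | 47 | 47 | 48 | 49 | 50 | 51 | 51 |
| Power at 0.90 (%) | 87.8 | 86.7 | 85.6 | 84.4 | 83.2 | 90.6 | 89.7 | 88.8 | 87.9 | 86.9 | 92.7 |

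Averaged over M with all assayed patients used, power is 0.867 and alpha 0.034. Stopping at the first 55 assayed gives 0.871 and 0.037. Either way it is about 87%.

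**The case against.** **The rule itself is correct.** This stands. At least 47 of 55 assayed patients gives what the plan claims, and the fault lies in how the 55 are obtained and defined.

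**The enrolment shortfall is one or two patients.** This also stands. Sixty matches the recruitment groups (30 breast, 10 ovarian, 20 lung), and a 10% planning figure is not accurate to one patient. Much of the loss of power comes from holding a discrete cut-off at 47. Enrolling 62 would raise the chance of reaching 55 only to 72%, and average power with a fixed 47 to 84%. That argues for a cut-off that follows the number assayed, rather than for leaving the text alone.

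**Withdrawals are not stated to be failures.** A reader might infer from the wording that patients lost before the assay count against feasibility, so that the trial has 26% power. The article does not say so. It speaks of a technically feasible rate and lists withdrawal as a separate allowance, and enrolling more than 55 makes sense only if 55 assessable patients were wanted. The 26% is therefore a worst case.

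**The last five patients are unused if nobody withdraws.** A reader might call this an error too. It is not one: a fixed n with its own cut-off is legitimate, and all 60 patients enter the comparison with controls.

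**The full protocol may define the evaluable set.** It may. But the article states the counting set, the threshold and the inflation explicitly, and those statements conflict with one another, so this is more than an omitted detail.

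**Conclusion.** The point holds in a limited form. The 47-of-55 rule has exact alpha 4.5% and power 90.6% among 55 assayed patients. Under the plan's own 10% loss, enrolling 60 gives 54 expected and only a 44% chance of reaching 55. With the cut-off fixed at 47, power is 83% at 54 assayed (alpha 2.4%) and about 74% averaged over withdrawals. The departure is towards a false verdict of not feasible; on none of these readings does alpha exceed 5%.

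The denominator of patients included contradicts the loss allowance and needs rewording, whichever reading was meant. Read literally, it would bring power to about 26% (alpha 0.2%).

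These figures take the 10% loss at face value, treat withdrawals as independent between patients, and assume that loss is unrelated to whether the assay would have worked. The article gives no observed loss rate.

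**What to change.** Rewrite the end of the feasibility paragraph:

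1. Define the denominator as patients with a baseline blood sample taken for the assay. Patients who leave before sampling are not counted; a sample that yields no result is a failure.
2. Replace the single threshold with the exact one-sided 5% binomial cut-off for the number obtained: 50:43, 51:44, 52:45, 53:46, 54:47, 55:47, 56:48, 57:49, 58:50, 59:51, 60:51, and the same rule below 50. State in advance whether all assayed patients or only the first 55 are used.
3. Correct the inflation: 60 enrolled with 10% loss give 54 expected, and 55 would need 55 / 0.9 = 61.1.
4. Restate power as about 83% at the expected 54 and about 87% averaged over withdrawals.

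The cost is a change to one paragraph and a less favourable power statement. The matched cut-offs do not restore 90%, and at exactly 54 the cut-off remains 47. No extra patients are needed. The change should be made before the assay results are known.

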## Discussion

The discovery of powerful biomarkers in cancer diagnosis and monitoring appears as a major challenge to improve patient’s care. Current research focuses on liquid biopsies that enable non-invasive detection of tumours, a clear advantage over tissues biopsies that have inherent risks. Blood samples are particularly interesting since this tissue contains cancer specific genetic material, proteins and extracellular vesicles. Tumour-derived exosomes emerge as a novel tool in cancer diagnosis and monitoring. However, most studies are focused on specific cancer subtypes, and no common marker is currently used, except CTCs. We have shown recently that human tumour cells, in contrast to their normal counterparts, release exosomes containing membrane-bound HSP70 [10]. Thus, we suggest that HSP70-exosomes could be used as a biomarker in the diagnosis and monitoring of most of cancers. For this purpose, we designed a pilot study, named ExoDiag, to demonstrate whether it is possible to detect and quantify HSP70-exosomes in blood in patients with solid cancers. We expected that HSP70-exosomes are highly secreted in the blood of patients suffering from different solid tumours (breast, ovarian and non-small cell lung cancer) when compared to healthy donors. A threshold corresponding to cancer detection will be determined. We will also investigate if the level of circulating HSP70-exosomes could be used for patient’s stratification. Furthermore, we will determine whether the level of circulating HSP70-exosomes changes upon treatment. Our aim is to establish whether HSP70-exosomes concentration is correlated to tumour regression or disease progression, thereby assessing their prognostic value in solid tumours. In long term, we hope to demonstrate that HSP70-exosomes could be a powerful tool to diagnose cancer and to guide clinicians in therapeutic decision-making, improving patient’s care.

To our knowledge, this will be the first study to evaluate the technical feasibility of measuring HSP70 in exosomes in cancer patients. The results of this pilot study might highlight the strong potential of liquid biopsy through exosomes in the monitoring disease progression. Therefore, if this pilot study is successful, an international multicentre study will be envisaged.

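### The patient-versus-control comparison is offered as confirming a cancer-specific marker, but it can only show that concentrations differ

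*Protocol article*

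**What the plan says.** Under Sample size and statistical analysis, after the feasibility calculation, the protocol article adds a second comparison: "baseline assays of the 60 patients will be compared with 20 controls, to confirm that exosome HSP70 is as a cancer specific marker". Its planning values start from the healthy donors: "The mean of HSP70 in the controls is expected to be 0". In patients the assumed mean is 2, and the SD is taken as 2 in both groups. At a two-sided 5% level the calculation concludes: "we will have a power of more than 95% to compare exosome HSP70 concentrations between cases and controls". No test is named.

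The Background shows what specificity means here. The authors report that "heat shock protein 70 is detected in the membrane of tumour-derived exosomes, in contrast to untransformed cells". The idea is presence with tumour and absence without it, which fits an expected control mean of 0.

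The exploratory paragraph at the end of the same section plans logistic regression and ROC curves, with AUC and 95% confidence interval, for treatment response. It then adds: "The same strategy will be applied to determine link between HSP70-exosomes concentration and the presence of metastases". Patients versus healthy donors is not among the contrasts named. The Discussion states that "A threshold corresponding to cancer detection will be determined", without giving a method or linking it to the comparison above.

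**The concern.** The purpose and the calculation answer different questions. Specificity is a property of the controls: they lack the marker, or fall below a cut-off. A comparison of concentrations has equality of the two groups as its null hypothesis, and rejecting it shows only that the groups differ. Two groups can differ clearly on average and still overlap so much that the marker separates them poorly.

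Read as written, a significant p-value would be reported as confirmation of a cancer-specific marker, and the power above 95% would be taken as the chance of showing specificity. Neither follows. The contrast on which specificity and a detection threshold would rest is also the one that the ROC plan does not name.

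**Working it through.** **Inputs** (Sample size and statistical analysis): 60 patients, 20 controls, means 2 and 0, common SD 2, two-sided alpha 5%.

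**1. The stated power.**
- Standard error of the difference: 2 × √(1/60 + 1/20) = 2 × 0.2582 = 0.516.
- Standardised signal: 2 / 0.516 = 3.873.
- Normal approximation: Φ(3.873 − 1.960) = Φ(1.913) = 97.2%.
- Two-sample t test (noncentral t, 78 df): 96.9%.
- With the protocol's 10% loss before the first assay (54 to 55 patients): 96.5% to 96.6% by the t test.
- Reading 60 as the total (40 versus 20): 95.5% by the normal approximation.

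All of these agree with the article's figure, which is not in dispute.

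**2. What the power depends on.** The signal is (patient mean − control mean) / [SD × √(1/60 + 1/20)]. The control mean enters only through the difference. Adding the same amount to both means leaves the statistic and the power unchanged, so the comparison does not test the expectation that controls are at 0.

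**3. What a significant result requires.** The t critical value on 78 df is 1.991, so the smallest significant observed difference is 1.991 × 0.2582 = 0.514 SD. With SD 2 that is about 1.03, or half the planned difference.

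**4. Overlap at the planning difference (illustration).** Assume normal data with equal SD and a difference of 2/2 = 1 SD.
- AUC = Φ(1/√2) = 0.76.
- Sensitivity at 95% specificity = Φ(1 − 1.645) = 26%.
- Sensitivity at 90% specificity = Φ(1 − 1.282) = 39%.
- Best balanced sensitivity and specificity = Φ(0.5) = 69% each.

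These figures depend on the normal model. With control mean 0 and SD 2, that model puts half of the controls below zero, which a concentration cannot be. Conversely, a non-negative quantity with mean exactly 0 has no spread, which conflicts with a common SD of 2. The planning values therefore do not fix an AUC. The illustration shows only that the planned difference is compatible with heavy overlap.

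**5. What 20 controls can say about specificity.** If all 20 are negative, the exact two-sided 95% lower limit is 0.025^(1/20) = 0.832, or 83%. For an AUC of 0.76 with 60 versus 20, the expected 95% interval is about 0.65 to 0.87.

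**The case against.** The case on the other side has several parts.

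- *This is a secondary comparison in a pilot.* The formal decision rule is feasibility (47 of 55), and the diagnostic claims in the Discussion are hedged. This stands and limits the weight of the point. However, the sentence on the comparison is not hedged: it promises confirmation and attaches a power to it, while the exploratory label is given only to the subgroup, treatment-response and metastasis analyses.
- *Control levels will be looked at anyway.* The primary endpoint in Study objectives and endpoints is the concentration in patients and in cancer-free controls, and the Discussion promises a detection threshold. This also stands, so it would be wrong to say that the controls will never be examined. The method for the threshold may be in the full protocol or SAP, and its absence from the article is not the fault. The fault is that the text names the concentration comparison as what confirms specificity.
- *No test is named.* True. The mean comparison is inferred from the planning inputs. A Welch or rank test would also be a test of difference and would not establish specificity either.

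A reader might infer something stronger: that the comparison would wrongly confirm specificity about 97% of the time when most healthy donors carry the marker. The documents do not support that. It requires control levels well above the expected 0, which would be an outside assumption. Where concentrations truly differ by the planned amount, rejecting equality is also correct, so the 97% is not a false-positive rate to set against 5%. Nor does the Discussion tie the envisaged international study to this p-value. It says only that the study would follow if the pilot succeeds.

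**Conclusion.** The concern holds as a mismatch between the claim and the analysis. The power figure is correct (about 97%, stated as more than 95%), but it is power to detect a difference in concentration, not to show specificity. That rests on the article's own wording and on the algebra of the comparison, and needs no assumption about control levels or distribution. The AUC of about 0.76 and the sensitivity of about 26% at 95% specificity hold only for normal data with the planning difference and SD, and should be read as illustration. No error rate is inflated. What is at risk is the conclusion drawn from a significant result. The change is worth making because it is nearly free and would also supply an analysis for the threshold announced in the Discussion.

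**What to change.** 1. In Sample size and statistical analysis, state the aim of the comparison as *to test whether HSP70-exosome concentrations differ between patients and controls at baseline*. Keep the power above 95% for that question only.
2. Extend the ROC strategy in the last paragraph of that section to patients versus controls: AUC with 95% confidence interval, plus the proportion of the 20 controls with quantifiable HSP70-exosomes and its exact 95% interval.
3. Base any statement about specificity, and the detection threshold in the Discussion, on these estimates. State the precision available: a lower 95% limit of 83% for specificity even if all 20 controls are negative.

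The cost is a change of wording and one extra analysis of data already planned, with no new participants or samples. The downside is a less favourable statement: a significant difference would no longer count as confirmation, and the specificity interval from 20 controls is wide.
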